### Association of Mental Illness Symptoms With the Severity of Acute COVID-19 

COVID-19 severity will be categorized according to the WHO classification [40]. The classification includes the following: mild illness (mild symptoms without the radiographic appearance of pneumonia); pneumonia (having symptoms and the radiographic evidence of pneumonia, with no requirement for supplemental oxygen); severe pneumonia (having pneumonia, including one of the following: respiratory rate >30 breaths/minute, severe respiratory distress, or blood oxygen saturation level ≤93% while at rest and breathing room air); and critical cases (eg, respiratory failure requiring invasive mechanical ventilation or nasal high flow oxygen, septic shock, other organ failure occurrence, or admission to the ICU).

### Statistical Analyses

The statistical analysis methodology is designed to align with the study’s defined objectives. All analyses will be conducted using SPSS (version 27; IBM Corp) and R (R Foundation for Statistical Computing) software. The analyses will be carried out in 5 phases, as outlined in Textbox 2.

The 5 phases of the statistical analyses carried out in this study.Phase 1: Characterization of the patient sample1.1. Sociodemographic analysis of the variables collected at T1 and the variables from the surveyed instruments at T2. This involves descriptive analysis, both univariate and bivariate, which will be differentiated by:1.1.1. Quantitative variables: mean and SD, coefficient of variation, and median and IQR1.1.2. Qualitative variables (nominal and ordinal categorical): analysis of distributions through absolute and relative frequencies, including absolute and relative accumulated frequencies1.1.3. Quantitative variables will be reported alongside appropriate tests for normal distribution to ensure the accuracy and validity of our statistical analyses.1.2. Bivariate and descriptive analysis using 2D tables will be calculated for all qualitative variables belonging to T1 with all instrument scores collected at T2: Chalder Fatigue Scale (CFQ-11), Hospital Anxiety and Depression Scale (HADS), 14-item Posttraumatic Stress Scale (PTSS-14) adapted to COVID -19, and EQ- 5D plus recorded COVID-19 symptoms. The previous points will be reiterated in this bivariate context, utilizing the computational aid of split->file categorical variables in situations where one variable is metric and the other is categorical.1.3. Internal consistency and reliability analysis of the T2 instruments: calculation of the Cronbach alpha (general and partial) for all ordinal items and item subgroups differentiated by the subscales defined by the respective authorsPhase 2: Determination of fatigue incidence caused by long COVID and its relationship with T1 and T2 variables2.1. Procedures for determining fatigue cutoff points in this cohort of patients:2.1.1. Bivariate analysis using optimal binning procedures for categorical variables (age class, sex, and BMI) with the total fatigue score, as well as partial scores of physical and psychological fatigue2.1.2. Multivariate analysis by constructing models in the format of decision trees via the CHAID (chi-square automatic interaction detection) algorithm [41], with total and partial fatigue scores as dependent variables2.2. Inferential analysis based on variables resulting from 2.1.1 and/or 2.1.2, considering the complexity of variables in T1 and T2:2.2.1. (1) Chi-Square tests to capture the association of categorical variables; (2) Shapiro-Wilk tests to verify the distribution of quantitative variables; (3) tests for comparing 2 or more population means: parametric analysis of variance (ANOVA) test and nonparametric (Kruskal-Wallis) test; and (4) correlation tests (Spearman or Pearson) to verify the degree of association between T2 instrument scalesPhase 3: Determination of patient groups based on fatigue differentiation3.1. Conducting classification analysis using clustering techniques, specifically the 2-step cluster analysis, to explore variables with greater power in differentiating groups of patientsPhase 4: Exploration of the best combination of T1 and T2 variables capable of discriminating patient fatigue levels through a discriminant multivariate analysisPhase 5: Investigation of the association between phase 3 groups and all T2 instrument scales using chi-square association tests

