**Methods:**

Using a consecutive nonrandom sampling technique, we will conduct a prospective cohort multicenter observational study in 5 Portuguese hospitals. Symptomatic adult patients with previous COVID-19 attending follow-up consultations will be enrolled. We will include patients who had mild, moderate, and severe acute disease. We will assess clinical outcomes related to COVID-19, including the type of respiratory support such as high-flow nasal cannula, noninvasive ventilation, and invasive mechanical ventilation. The exclusion criteria will include previous severe psychiatric disorders confirmed by a psychiatrist; refusal or inability to respond to the questionnaire; concomitant neurological disorder; persistent fatigue symptoms during the 6 months before infection; and the need for invasive mechanical ventilation during COVID-19 infection due to a high prevalence of postintensive care syndrome. Our primary outcome is the prevalence of fatigue in patients with post–COVID-19 depression and/or anxiety, as measured by the Chalder Fatigue Scale (CFQ-11) and the Hospital Anxiety and Depression Scale (HADS). The secondary outcomes will include an assessment of health-related quality of life via the EQ-5D questionnaire and an exploration of the prevalence of symptoms of posttraumatic stress disorder (PTSD) using the 14-item Posttraumatic Stress Scale (PTSS-14). We will also examine the association between mental health symptoms and the severity of acute COVID-19. The post–COVID-19 data will be collected at least 6 months after the positive test and no longer than 9 months during the clinical appointment.

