### Primary Outcome

#### Fatigue

A validated fatigue assessment tool will be used at the follow-up visit to capture a broader range of participants. This will provide a more comprehensive understanding of the relationship between fatigue and mental symptoms in individuals with long COVID. Fatigue will be measured using the CFQ-11 [26]. This is an 11-item self-report measure of physical and mental fatigue. Participants rate their fatigue experienced over the past month compared to their usual energy levels using a 4-point Likert scale ranging from 0 (“less than usual”) to 3 (“much more than usual”) [29]. Scores range from 0 to 33. A bimodal version can also be calculated, where scores range from 0 to 11, with a cutoff score of 4 or more indicating a case of fatigue [29]. Reliability coefficients for the CFQ-11 have been shown to range between 0.8 and 0.9 [29-31] in both patients with chronic fatigue and the general population. This study will use only the Likert scale to reduce the risk of ceiling effect bias.

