### Secondary Outcomes

#### Depression and Anxiety

Symptoms of depression and anxiety will be assessed using the HADS [27], a practical, validated tool for assessing symptom severity in anxiety and somatic disorders in psychiatric and primary care settings and the general population [32]. This measure comprises 14 items, 7 measuring symptoms of anxiety and 7 measuring symptoms of depression. The scores are categorized into different ranges: 0 to 7 as “normal,” 8 to 10 as “mild,” 11 to 14 as “moderate,” and 15 to 21 as “severe.” The HADS questionnaire has been validated in many different languages and settings [32-34].

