
### Power and Sample Size

We plan to conduct a prospective multicentric observational study to investigate the prevalence and severity of mental illness symptoms and fatigue in individuals with long COVID. Based on previous studies and expert opinion, we expect the prevalence of fatigue and mental symptoms in this population to be around 50% [42,43]. We aim to detect a minimum effect size of 0.2 with a power of 80% and a significance level of *P=.*05.

Using these assumptions, we performed a sample size power analysis using a 2-sample *t* test. We found that a total sample size of 200 participants (100 with adverse mental health symptoms and 100 without) would be required to detect the minimum effect size of 0.2 with 80% power and a significance level of *P=*.05. The required sample size was calculated using an a priori power analysis with an online calculator [44]. To compensate for a projected 25% loss to follow-up, we aimed for 250 participants.

We plan to recruit participants from multiple hospitals and primary care centers across Portugal, focusing on individuals who have been diagnosed with long COVID and are experiencing mental illness symptoms and/or fatigue. Recruitment will be closely monitored throughout the study to assess the pace at which participants are enrolled. The need for sample size adjustment will be determined based on the observed recruitment rates and the accumulating data. We plan to conduct an interim analysis after the recruitment of the first 100 patients.

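### Phase 5 names only chi-square for comparing the cluster groups on all T2 scales, which discards the order of numeric scores when Phase 2 already lists better tests

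*Protocol article*

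**What the plan says.** Textbox 2 of the Protocol article sets out five phases. Phase 3 forms patient groups by two-step cluster analysis. Phase 5 then relates those groups to the questionnaires: "Investigation of the association between phase 3 groups and all T2 instrument scales using chi-square association tests". No other test is named for that step, and the text does not say whether scores are to be banded first.

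The T2 instruments are the CFQ-11, HADS, PTSS-14 and EQ-5D. For the CFQ-11, "Scores range from 0 to 33", and the Fatigue section says that only the Likert scoring will be used, not the bimodal version. Each HADS subscale runs to 21, with four ordered bands. The PTSS-14 is a summed total with a cutoff of 45. The EQ-VAS runs from 0 to 100.

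Phase 2, step 2.2.1, is more differentiated. Item (1) is "Chi-Square tests to capture the association of categorical variables". Item (3) is "tests for comparing 2 or more population means: parametric analysis of variance (ANOVA) test and nonparametric (Kruskal-Wallis) test". Item (4) gives Spearman or Pearson correlation between T2 scales.

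**The concern.** Pearson chi-square gives the same P value however the score values are shuffled. Applied to a numeric score, it tests for any difference between unlabelled columns and cannot concentrate on one group scoring higher than another. Its degrees of freedom grow with the number of distinct scores, and expected counts become small.

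Phases 2 and 5 therefore treat the same kind of comparison, a score across groups, in different ways, and Phase 5 takes the weaker route. At stake is a real difference between patient groups in anxiety, depression, PTSD symptoms or quality of life being reported as no association. If raw scores are tabulated, the P values would also rest on an approximation that fails in sparse tables.

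**Working it through.** **Inputs from the Protocol article.** N = 200 analysed and alpha 0.05 (Power and Sample Size); the score ranges above; the Phase 5 test. Two-sided testing is assumed.

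**The plan's own figure.** No power is stated for Phase 5. The stated total of 200 is for a two-sample t test with effect size 0.2 and 80% power. Read as a standardised difference, that needs 2 x (1.96 + 0.84)^2 / 0.2^2 = 2 x 7.85 / 0.04, or about 393 per group, and 100 per group gives 29% power. So 200 does not reproduce on that reading. That is a separate matter, and 200 is used here only as the planned size.

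**Step 1: table sparsity (no effect size needed).** Average expected count with two groups = 200 / (2 x number of possible values):
- HADS subscale, 22 values: 200/44 = 4.5
- CFQ-11, 34 values: 200/68 = 2.9
- EQ-VAS, 101 values: 200/202 = 1.0

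Values that nobody scores would raise these averages; more clusters would lower them.

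**Step 2: cost of the extra degrees of freedom.** Take an ordered effect that a 1-df test detects with 80% power, with noncentrality (1.96 + 0.84)^2 = 7.85. At that noncentrality, chi-square power is 64.5% on 3 df, 44.6% on 9 df, 31% on 20 df and 18% on 60 df. Two groups by 22 HADS values would have 21 df, and by 34 CFQ-11 values 33 df.

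**Step 3: simulation of the Phase 5 comparison.** N = 200, 2 or 3 groups, 1,000 runs per setting. The difference d between the extreme groups is in SD units. The value of d and the score means and SDs are assumptions. Power in %, at d = 0.4 / 0.5 / 0.6:

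| Score, groups | Raw chi-square, d = 0 | Raw chi-square | Banded chi-square | Kruskal-Wallis |
|---|---|---|---|---|
| HADS, 2 | 4.4 | 23.6 / 43.4 / 63.3 | 56.6 / 72.1 / 88.0 | 80.6 / 93.1 / 98.2 |
| HADS, 3 | 4.3 | 9.9 / 17.5 / 29.1 | 28.9 / 42.5 / 62.9 | 48.7 / 69.6 / 86.8 |
| CFQ-11, 2 | 2.6 | 11.4 / 22.4 / 39.4 | 56.6 / 77.3 / 91.4 | 78.8 / 91.4 / 98.8 |
| CFQ-11, 3 | 2.9 | 7.0 / 8.1 / 14.3 | 31.0 / 45.1 / 63.5 | 49.6 / 71.8 / 84.2 |
| PTSS-14, 2 | 1.2 | 6.7 / 9.7 / 19.2 | 57.2 / 78.4 / 91.5 | 78.5 / 92.9 / 98.7 |
| PTSS-14, 3 | 1.5 | 2.3 / 3.9 / 5.6 | 28.2 / 45.7 / 61.5 | 48.8 / 68.5 / 83.6 |

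ANOVA was close to Kruskal-Wallis throughout. Under no difference, Kruskal-Wallis rejected in 4.3 to 5.7% of runs and banded chi-square in 4.0 to 5.7%.

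**Step 4: losses against Kruskal-Wallis.**
- Raw scores: smallest 98.2 - 63.3 = 34.9 points (HADS, 2 groups, d = 0.6); largest 92.9 - 9.7 = 83.2 (PTSS-14, 2 groups, d = 0.5).
- Banded scores: smallest 98.7 - 91.5 = 7.2 (PTSS-14, 2 groups, d = 0.6); largest 69.6 - 42.5 = 27.1 (HADS, 3 groups, d = 0.5).
- At d = 0.2 every test is weak, and the losses are 12 to 27 points (raw) and 5 to 14 points (banded).

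**The case against.** The strongest reply is that raw-score tabulation is stated nowhere, and that the article supplies categories: the HADS bands, the PTSS-14 cutoff, the fatigue cutoffs to be derived in step 2.1 and the three-level EQ-5D items. Chi-square on those categories across nominal clusters is valid. This stands in part. It makes the raw-score figures the unfavourable end of the range. But Phase 5 says scales and does not mention bands, and banding still costs power for no gain in this comparison.

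A second reply is that if the clusters are built from the same T2 scales, power is not the main problem. That is right. The groups would differ on those scales by construction, and no choice of test repairs it. Phase 3 does not list its inputs, but its title refers to differentiation by fatigue, so the CFQ-11 is a likely one. The choice of test matters for scales left out of the clustering.

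A third reply is that the primary question is untouched. As a comparison of fatigue prevalence with and without depression or anxiety it is a 2x2 table, where order plays no part. This stands.

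A reader might also infer that acute severity against mental symptoms will be tested by chi-square, with a similar loss. The abstract says "We will also examine the association between mental health symptoms and the severity of acute COVID-19", and the severity section says "COVID-19 severity will be categorized according to the WHO classification" into four ordered classes, but neither names a test. Item (1) of step 2.2.1 concerns categorical variables only, step 2.2 is introduced as inference on the variables that come out of the binning and CHAID steps, and item (3) fits a HADS or PTSS-14 score compared across severity classes. The absence of a named trend test in a condensed article is not an error.

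**Conclusion.** The point holds for Phase 5. The stated test is poorly matched to ordered scores, and better tests already stand in Phase 2. The loss is about 35 to 83 points on raw scores, with type I error of about 1 to 3% for CFQ-11 and PTSS-14, and about 7 to 27 points on banded scores. These figures assume N = 200, 2 or 3 groups and a 0.4 to 0.6 SD difference between the extreme groups. The direction of the loss follows from ignoring order, but its size depends on those assumptions.

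No single loss figure covers the whole plan, and nothing here shows that severity against HADS will be analysed by chi-square. The most that can be said about severity is that Kruskal-Wallis, the listed test that fits, does not use the order of the classes. At N = 200 it had 54 to 57% power against 67 to 73% for Spearman at an assumed correlation of 0.2 (a gap of roughly 10 to 20 points), and 91 to 93% against 97 to 98% at 0.3 (about 5 points).

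**What to change.** In Phase 5, replace the chi-square tests with Kruskal-Wallis or ANOVA for comparing scale scores between the Phase 3 groups, in line with item (3) of step 2.2.1. Keep chi-square for nominal variables.

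State which variables enter the Phase 3 clustering. Report any T2 scale among them descriptively by cluster, without a P value, because testing it against those clusters is circular.

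As an optional gain, analyse WHO severity against HADS and PTSS-14 scores by an ordered test such as Spearman or Jonckheere-Terpstra.

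The cost is wording in the analysis plan. The Phase 5 tests are already listed, and no data collection changes. The ordered severity test has one small downside: less power for a non-monotone pattern, which the descriptive cross-tables would still show.

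### Phase 5 tests the fatigue-based clusters from Phase 3 against every T2 scale, including the CFQ-11 that defines fatigue, so the P value for any clustering input is circular

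*Protocol article*

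**What the plan says.** The analysis has five phases (Textbox 2, Statistical Analyses). Phase 3 defines patient groups by how they differ in fatigue. Its method is "Conducting classification analysis using clustering techniques, specifically the 2-step cluster analysis", used to find the variables that best separate groups of patients. The clustering inputs are not listed and the number of clusters is not fixed.

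On the measure itself, the Fatigue section says: "Fatigue will be measured using the CFQ-11". The CFQ-11 is a T2 instrument: Data Collection places it at the second visit, and Phase 1.2 cross-tabulates the T1 variables "with all instrument scores collected at T2: Chalder Fatigue Scale (CFQ-11), Hospital Anxiety and Depression Scale (HADS), 14-item Posttraumatic Stress Scale (PTSS-14", then continues to the EQ-5D.

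Phase 5 is stated in one line: "Investigation of the association between phase 3 groups and all T2 instrument scales using chi-square association tests". It does not exclude scales used in the clustering, use a hold-out sample, or label the results as descriptive only.

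**The concern.** A clustering algorithm places its boundaries where patients differ most on the input variables. Groups built this way differ on those variables even when the data come from one homogeneous population. The usual null distribution of the chi-square statistic assumes that group membership was not chosen by looking at the variable under test. For a clustering input that assumption fails, and a small P value shows only that the algorithm worked.

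On the plain reading this applies to the CFQ-11: the groups are fatigue groups, and the scope of Phase 5 takes in the fatigue scale. It extends to any other T2 scale that enters the clustering.

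What is at stake is interpretation. The research questions in Textbox 1 concern the links of fatigue with depression, anxiety, PTSD symptoms and quality of life, and the article expects a significant link. Phase 5 is the last step and could be cited as confirming that link, with valid and circular P values side by side in one table.

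**Working it through.** **Plan's own figure.** The protocol states no error rate, power or cluster number for Phase 3 or Phase 5, so there is nothing to reproduce. From Power and Sample Size come only the sizes, 200 analysed ("a total sample size of 200 participants (100 with adverse mental health symptoms and 100 without) would be required") and 250 enrolled ("To compensate for a projected 25% loss to follow-up, we aimed for 250 participants"), and the 5% level ("with 80% power and a significance level of *P=*.05"). Whether 200 suits its own purpose is a separate question; nothing here depends on it.

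**Why an input is almost always significant.** Take 200 patients, one input and two clusters. If the cluster boundary falls at the median, the 2×2 table of cluster by median split is 100/0 and 0/100. For a 2×2 table, chi-square = N(ad − bc)² / (product of the four margins) = 200 × (100 × 100)² / (100 × 100 × 100 × 100) = 200, against a 5% critical value of 1.96² = 3.84. Now suppose the boundary misses the median and 20 patients above the median fall in the lower cluster. The rows become 100/0 and 20/80, and chi-square = 200 × (100 × 80 − 0 × 20)² / (100 × 100 × 120 × 80) = 200 × 64,000,000 / 96,000,000 = 133. No real structure is needed.

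**Why a non-input is safe.** Cluster labels are a function of the inputs alone. If a scale is independent of the inputs, it is independent of the labels, and the chi-square test keeps about its nominal level.

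**Simulation under the null.** Five mutually independent normal scores (CFQ-11, HADS-A, HADS-D, PTSS-14, EQ-5D) were drawn from one population, for N = 200 and 250, with 500 runs per setting. Assumptions not in the protocol:
- k-means stands in for two-step clustering, with two or three clusters imposed;
- CFQ-11, PTSS-14 and EQ-5D are split at the median, and the HADS scores are cut into four bands at the 50th, 75th and 90th percentiles;
- the input sets are those shown in the table; T1-type variables are two further independent scores.

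Rejection rates at nominal 5%, as ranges over the settings:

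| Clustering inputs | CFQ-11 | Each other T2 scale |
|---|---|---|
| CFQ-11 only | 100% | 3.4% to 7.6% |
| CFQ-11 + two T1-type variables | 83% to 99% | 4.2% to 6.6% |
| All five T2 scores | 76% to 95% | 72% to 96% |
| All five T2 scores + two T1-type variables | 70% to 91% | 68% to 91% |
| T1-type variables only | 4.4% to 7.0% | 3.4% to 6.6% |

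The Monte Carlo standard error at 5% is √(0.05 × 0.95 / 500) ≈ 1.0 percentage point, so the low figures are about nominal. With all T2 scores as inputs, at least one scale was significant in every run. The dividing line throughout is whether the tested scale was a clustering input.

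**The case against.** **The mental-health scales may be untouched.** A reader might infer that the Phase 5 associations with HADS, PTSS-14 and EQ-5D arise by construction. The document does not support that. It lists no clustering inputs; the Phase 3 heading points to fatigue, and the aim of finding the variables that separate groups best leaves room for others without naming any. If the CFQ-11 is the only T2 input, with or without T1 variables, the other scales are tested at about 5%. This objection stands, and it limits the certain part of the point to the CFQ-11.

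**Phase 5 is not the only test.** Phase 2.2.1 already plans correlations between the T2 scales, which do not depend on the clusters and bear directly on the research questions. This also stands and limits the harm.

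**Chi-square is not wrong in itself.** A reader might infer that it cannot be used on scale scores. The protocol supplies HADS bands, a PTSS-14 cutoff of 45, three-level EQ-5D items and, from Phase 2.1, fatigue cutoffs. Chi-square on such categories is valid; it only loses information relative to a test on the scores.

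**An article condenses.** The input list and the number of clusters may properly sit in a fuller plan. What the article itself fixes is the scope of Phase 5, namely all T2 scales, and a fuller plan would have to change that wording rather than add to it. This part of the objection does not remove the point.

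**Conclusion.** The point holds in limited form. Following the text as written gives a circular P value for the CFQ-11 and for any other T2 scale that enters the clustering. Under the stated null, false rejection for the CFQ-11 is 100% as sole input and 83% to 99% with two T1-type variables added. For HADS, PTSS-14 and EQ-5D the range runs from about 5% (not inputs) to 68% to 96% (inputs), and the protocol does not say which case applies. It would be wrong to conclude that Phase 5 must manufacture the link between fatigue and mental health.

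The exact rates depend on the assumed number of clusters, categories and input sets, and on k-means as a stand-in. The direction does not: every input was rejected far above 5% in every setting. The figures assume at least two clusters; if automatic selection returned one, there would be no Phase 5 test. If only T1 variables formed the groups, the problem would vanish, but that does not fit groups defined by fatigue.

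**What to change.** - **Phase 3:** list the clustering inputs in advance. A clean choice is the CFQ-11 physical and psychological subscores only.
- **Phase 5:** replace the scope of all T2 scales with T2 scales not used to form the Phase 3 groups. With the choice above, these are HADS-A, HADS-D, PTSS-14, the EQ-5D index and EQ-VAS.
- **Inputs:** report the CFQ-11, and any other scale used in the clustering, by cluster descriptively and without P values.
- **Optional:** for scale scores, use the ANOVA or Kruskal-Wallis tests already named in Phase 2.2.1 instead of chi-square on categories. This gains efficiency and is not a correction.

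In the simulation, with the CFQ-11 as the only clustering input, the remaining scales were rejected in 3.4% to 7.6% of runs, about nominal. The cost is a change of wording, with no new data, visits or patients. The downside is fewer P values in an exploratory phase. The Phase 2.2.1 correlations between T2 scales are unaffected.
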